# Sacral neuromodulation for constipation and fecal incontinence in children and adolescents – study protocol of a prospective, randomized trial on the application of invasive vs. non-invasive technique

**DOI:** 10.1186/s13063-024-08052-6

**Published:** 2024-03-22

**Keywords:** Sacral neuromodulation, Sacral nerve stimulation, Enteral neuromodulation, Functional constipation, Chronic refractory constipation, Hirschsprung’s disease, Fecal incontinence

## Abstract

**Background:**

A therapeutic effect of sacral neuromodulation (SNM) on fecal incontinence (FI) and quality of life has been proven in adults. SNM is, however, rarely used in pediatric cases. The aim of the study is to investigate effects of SNM in pediatric constipation in a prospective parallel-group trial.

**Methods:**

A monocentric, randomized, unblinded, parallel-group trial is conducted. SNM is conducted in the invasive variant and in an innovative, external approach with adhesive electrodes (enteral neuromodulation, ENM). We include patients with constipation according to the ROME IV criteria and refractory to conventional options. Patients with functional constipation and Hirschsprung’s disease are able to participate. Participants are allocated in a 1:1 ratio to either SNM or ENM group. Clinical data and quality of life is evaluated in regular check-ups. Neuromodulation is applied continuously for 3 months (end point of the study) with follow-up-points at 6 and 12 months. Findings are analyzed statistically considering a 5% significance level (*p* ≤ 0.05). Outcome variables are defined as change in (1) episodes of abdominal pain, (2) episodes of FI, (3) defecation frequency, (4) stool consistency. Improvement of proprioception, influence on urinary incontinence, quality of life and safety of treatment are assessed as secondary outcome variables. We expect a relevant improvement in both study groups.

**Discussion:**

This is the first trial, evaluating effects of neuromodulation for constipation in children and adolescents and comparing effects of the invasive and non-invasive application (SNM vs. ENM).

**Trial registration:**

The study is registered with clinicaltrials.gov, Identifier NCT04713085 (date of registration 01/14/2021).

**Supplementary Information:**

The online version contains supplementary material available at 10.1186/s13063-024-08052-6.

## Background

Sacral neuromodulation (SNM) has been proven to reduce fecal incontinence (FI), and to improve quality of life in adult patients [1]. Low-intensity electrical charges are placed in contact with the target nervous tissue to achieve pulsed depolarization of axons [2]. However, evidence-based knowledge on mechanisms of action and efficacy is still limited. It has been postulated that SNM primarily affects afferent nerve activity [2]. Beyond that, regions of learning in the central nervous system and even their neuroplasticity are sought to be affected [3].

Despite these limitations in the understanding of its mode of action, SNM is established as surgical treatment option in adult patients because of its clinical efficacy [4]. As a minimally invasive approach, it is applied in patients with refractory urological and proctological conditions. Small, rechargeable, and magnetic resonance imaging-safe devices have made the implantation suitable even for children and adolescents. However, SNM is currently only used in highly selected pediatric cases, which does not answer the need for further therapies in refractory cases. Promising results of singular case studies and very small population studies have not yet been transferred to prospective case–control trials to gain evidence-based results. Furthermore, a non-invasive SNM option was developed to offer a quick, cost-effective, and child-friendly approach. Positive effects of SNM on functional constipation in children who continue to be treated conservatively could have been observed [5], while they remain controversial in adults [6, 7]. In a review of 2011, Pauwels et al. observed no significant improvement of constipation in most of the included studies and proposes to apply SNM only in adult patients, refractory to treatment in order to potentially avoid more invasive treatment options [8]. Long-term outcomes of Gortazar de las Casas and colleagues revealed an efficacy of 38% in adult patients within a follow-up time of 5 years [9]. However, we see the justification of a potential efficacy of SNM on pediatric constipation due to the following point: We support the hypothesis of a unifying dysfunction of the enteral nervous system [10], which might even more connect functional/slow-transit-constipation (FC), rectal evacuation disorders, congenital neuro-intestinal dysfunctions with heterogeneous symptoms of constipation and fecal incontinence in children and adolescents. Indication for SNM in children and adolescents might therefore be discussed further.

There is currently a lack of randomized trials that are adequately powered and apply validated outcome measures, to allow for firm recommendations on the use of SNM in pediatric patients. We report a protocol of a monocentric, randomized, unblinded, parallel-group trial of SNM in pediatric and adolescent patients with symptoms of refractory chronic constipation.

## Materials and design

### Study objective and hypotheses

The aim of the study is to investigate the effects of SNM on symptoms and quality of life in children and adolescents. We intend to demonstrate that SNM is safe and effective in treatment of constipation and FI refractory to conventional therapeutic options.

The following hypotheses will be investigated within 3 months of treatment:(A)SNM is superior to ENM regarding treatment of abdominal pain as main symptom of refractory chronic constipation in childhood and adolescence.(B)Further exploratory hypotheses will be evaluated:SNM/ENM is effective and safe in reducing symptoms of chronic constipation and FI in children and adolescents as an additional therapeutic approach while continuing conventional treatment options unchanged.SNM/ENM treatment is effective in the subgroup of patients with Hirschsprung’s disease (HD).

### Technique

#### Enteral neuromodulation (ENM)

ENM is administered non-invasively via two cutaneous adhesive electrodes, placed paravertebrally and periumbilically (Fig. 1). The stimulation is applied with a frequency of 15 Hz and a pulse width of 210µs. Detailed stimulation techniques have been described previously [5] and are administered via a pulse generator (Ostimex® ProfiPlus TENS/EMS 335035) [11]. The adhesive electrodes (50 × 50mm in size) have a conductive surface and adhere to the skin by themselves. The manufacturer makes multiple use possible.

**Fig. 1 Fig1:**
[figure not shown]
Enteral neuromodulation. Placement of the cutaneous adhesive electrodes of this non-invasive approach is depicted: the electrical field is built between a paravertebrally and periumbilically placed electrode

#### Sacral neuromodulation (SNM)

SNM is applied via two surgical interventions. First, the flexible electrode lead with four equally spaced electrode contact points (quadripolar tined lead electrode, Medtronic Interstim, Fig. 2A) is inserted percutaneously via the sacral foramen close to the sacral spinal nerve S3 or S4. A motor or sensory response can be monitored directly intraoperatively by probatory electrical stimulation and determines the side of the final implantation of the tined electrode. Stimulation is generated externally by a pulse generator and will be started on the first postoperative day with a frequency of 14 Hz and a pulse width of 210µs. The bipolar electrical field is generated between different poles of the tined lead, directly located at the sacral spinal nerves.

**Fig. 2 Fig2:**
[figure not shown]
Sacral neuromodulation. Figure 2 illustrates the surgical implantation of sacral neuromodulation. **A** The tined lead electrode is placed at the sacral spinal nerve S3 or S4. **B**, **C** The previously implanted electrode is connected to a pulse generator, which is then implanted subcutaneously above the gluteal region

After a successful trial phase with a neuronal response, an implanted pulse generator (IPG, Medtronic® Interstim Micro) is connected to the implanted electrode (Fig. 2B) and subcutaneously implanted (Fig. 2C) 4 weeks after the electrode’s implantation to secure optimal electrode positioning and exclusion of postoperative complications.

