### Trial design

This is a monocentric, randomized, unblinded, 2-arm parallel-group trial in a 1:1 allocation ratio. The study is conducted at the University Hospital Erlangen, Friedrich-Alexander-Universität Erlangen-Nürnberg (FAU) from 2019 to 2023. Potential subjects are screened among patients attending pediatric surgical and pediatric gastroenterological clinics. Diagnoses are made according to the ROME IV criteria for FC [12]. Interventions are provided to subjects based on their group assignment of either 3 months of SNM or ENM therapy. Regular checkups and a follow up appointment are conducted within the trial and after 6 and 12 months after the initiation of the intervention. All participants are informed of the purpose of the study and obtain their informed consent before participating in this parallel group study. The subjects may choose to withdraw from the study, or they may be withdrawn from the study, at any time at the discretion of the investigator. If a subject withdraws or is withdrawn, every effort is made to complete and report the observations. The study design is presented in Fig. 3.

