#### Group 1: enteral neuromodulation

ENM is continuously applied for 12 weeks in each patient. Stimulation intensity is individually set by each patient to achieve a comfortable stimulation below pain threshold.

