#### Group 2: sacral neuromodulation

With the implantation of the electrode, stimulation of S3/4 is continuously applied. Patients are able to set stimulation intensity parameters within a preset range via an external device with or without the IPG.

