### Study outcomes

Participants are required to complete bowel movement diaries throughout the trial to the first target point. Children aged up to 7 years are thereby represented by their next-of-kin, whereas participants ≥ 13 years of age are advised to fill in the questionnaires by themselves. Between age 8 to 12, documentation is conducted together and depending on the child’s autonomy. At routine check-ups at baseline, 4 weeks, 3 and 6 and 12 months, specialized questionnaires must be completed. Quality of life analysis is conducted at baseline and after 3, 6 and 12 months, as described below (Fig. 4).

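### Only the SNM arm has a step after randomisation that a child may not pass before month 3, and a discretionary exclusion rule could remove those children from the primary comparison

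*Protocol article*

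**What the plan says.** All references are to the protocol article.

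- **Technique, Sacral neuromodulation (SNM).** SNM takes two operations. The second is conditional: "After a successful trial phase with a neuronal response, an implanted pulse generator" is connected to the electrode and implanted 4 weeks after it. The interval serves "to secure optimal electrode positioning and exclusion of postoperative complications". No pain or bowel threshold is attached to the word successful.
- **Group 1: enteral neuromodulation.** "ENM is continuously applied for 12 weeks in each patient", with no condition.
- **Trial design.** "Interventions are provided to subjects based on their group assignment of either 3 months of SNM or ENM therapy". Subjects may withdraw or be withdrawn at the investigator's discretion, and then "every effort is made to complete and report the observations".
- **Group 2: sacral neuromodulation.** Stimulation runs from electrode implantation, and patients adjust intensity "within a preset range via an external device with or without the IPG".
- **Statistical analysis.** Missing follow-up values are filled by last observation carried forward (LOCF). Separately, a child with much missing data is excluded if the project management group so decides. No amount of missing data is fixed as the trigger.
- **Study outcomes.** Participants "complete bowel movement diaries throughout the trial to the first target point", and check-ups include week 4 and month 3.

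**The concern.** Hypothesis A is that SNM is superior to ENM for abdominal pain within 3 months. The generator step comes after randomisation, exists in one arm only and falls before that endpoint. The sections on trial design and Group 2 do not say how a child without a generator proceeds from week 4 to month 3.

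That gap meets a stated rule that can remove children. A child who declines the operation after allocation, or stops before the generator, is a natural candidate for withdrawal or for the missing-data exclusion. The trial is open label, the project management group is headed by the principal investigator, and the protocol does not say that the group decides without sight of the arm. If such children are removed, and if they would have done worse on pain, the remaining SNM group is selected while the ENM group is not. The resulting error favours the hypothesis under test. It could not be repaired later if those children's month-3 data were never collected.

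**Working it through.** **1. The plan's own figure.** The Sample size calculation gives 39 per group for a 30% difference, alpha 0.05 and power 80%, without the rates per arm. With assumed rates of 50% and 80% (mean 0.65), two-sided:

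n = [1.96·√(2·0.65·0.35) + 0.8416·√(0.50·0.50 + 0.80·0.20)]² / 0.30² = (1.322 + 0.539)² / 0.09 ≈ 38.5, so 39 per group.

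This reproduces the figure, with power 80.5%. No allowance for losses is stated.

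**2. Inputs for the selection effect.**
- From the protocol: 39 per arm, chi-square test, p < 0.05 (two-sided assumed).
- Assumed, because the protocol gives no value: true success p = 50% or 60%, equal in both arms; share g = 10, 20 or 30% of SNM children not reaching the generator, all dropped; their own success rate q.

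**3. Formula.** Apparent success among the SNM children who remain:

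p_S = (p − g·q) / (1 − g), with n_S = 39·(1 − g), rounded to 35, 31 and 27.

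Example with p = 0.50, g = 0.20, q = 0.25: (0.50 − 0.05) / 0.80 = 0.5625, a spurious gain of 6.25 points.

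**4. Chance of a significant result in favour of SNM when the arms are equal** (exact binomial enumeration, chi-square without continuity correction; ENM n = 39):

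| p | g | n_S | p_S, none respond (q = 0) | False SNM win | p_S, q = p/2 | False SNM win |
|---|---|---|---|---|---|---|
| 50% | 10% | 35 | 55.6% | 6.8% | 52.8% | 4.2% |
| 50% | 20% | 31 | 62.5% | 17.4% | 56.3% | 7.2% |
| 50% | 30% | 27 | 71.4% | 41.3% | 60.7% | 13.0% |
| 60% | 10% | 35 | 66.7% | 8.5% | 63.3% | 4.8% |
| 60% | 20% | 31 | 75.0% | 25.4% | 67.5% | 8.9% |
| 60% | 30% | 27 | 85.7% | 63.6% | 72.9% | 18.5% |

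With all 39 SNM children kept, the chance is 2.7% (p = 50%) or 2.5% (p = 60%).

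**5. When there is no bias.** If the step is unrelated to pain (q = p), then p_S = p and the chance stays at about 2.4 to 2.5%. Dropping those children then costs only power: for 50% against 80% it falls from 80.5% to 78.1, 75.0 and 71.2% at g = 10, 20 and 30%.

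**The case against.** The strongest reply has four parts.

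- **The step is not a symptom test.** It is a neuronal response, with positioning and complication checks. A reader might infer that SNM is reduced to pre-selected responders. The text does not support that, and the link between this step and a 50% fall in pain episodes is unknown. This part stands.
- **No generator need not mean no SNM.** Stimulation begins with the electrode and is adjustable "within a preset range via an external device with or without the IPG". A reader might infer that failures leave the assigned therapy. The protocol does not say so. Equally, it does not say that such a child continues external stimulation to month 3, so the gap remains.
- **The stated rules lean towards retention.** Observations are to be completed after withdrawal, and LOCF has a week-4 value to use. The treatment rule alone therefore does not produce a selected group. However, the exclusion rule sits beside LOCF with nothing to say which applies. A child who never has the electrode placed has no on-treatment value to carry. The exclusion rule covers both arms, but the step that feeds it exists in one.
- **Analysis sets may be defined elsewhere.** The article condenses a fuller protocol, and a missing analysis-set statement alone would be no finding. The point rests on a rule that the article does state.

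Two further limits apply. Follow-up timed "after 6 and 12 months after the initiation of the intervention" might suggest that a child who never starts has no month-3 visit. That wording covers the 6- and 12-month appointments, so it does not touch hypothesis A. Consent to the treatment modalities also precedes randomisation, which should reduce later refusals of surgery but does not rule them out.

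**Conclusion.** The concern holds as an open route to bias, not as a demonstrated one. A step that exists only in the SNM arm, an undescribed path for children who do not pass it, and an exclusion rule without a threshold together allow SNM children to be removed from the month-3 comparison with no ENM counterpart.

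Under the assumptions above, with every such child dropped, the false-superiority chance is 4.2 to 18.5% under moderate selection and 6.8 to 63.6% in the worst case, where none of them would have responded. The worst case should not be read as the expected result: no document supports a failure rate, a response rate or full exclusion. If nobody is dropped, or the step is unrelated to pain, there is no inflation.

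**What to change.** 1. In Statistical analysis, replace the discretionary exclusion, for the month-3 abdominal pain comparison, with analysis of every randomised child in the assigned arm.
2. In Study outcomes, state that the diary and questionnaires continue to month 3 whether or not the electrode or generator is implanted.
3. Report the number of SNM children not reaching the generator, and label any comparison limited to generator recipients as supportive.
4. Reconcile the SNM technique, Trial design and Group 2 sections on what SNM children without a generator receive. The content of that clinical rule is for the investigators.
5. Keep the stated LOCF rule if wished, and add a sensitivity analysis that counts unobtainable month-3 pain data as not successful.

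**Cost.** Wording changes and slightly more data collection. The reported SNM response may be lower, and power with it. As an extreme illustration, if all children not reaching the generator were non-responders and 80% of the others succeeded, the SNM rate would be 0.80·(1 − g) = 72, 64 or 56% at g = 10, 20 or 30%. Power against 50% with 39 per arm would then be about 51, 24 or 8%. That would reflect a smaller true effect of assignment to SNM, which is what families choosing surgery need to know.

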### Trial design

This is a monocentric, randomized, unblinded, 2-arm parallel-group trial in a 1:1 allocation ratio. The study is conducted at the University Hospital Erlangen, Friedrich-Alexander-Universität Erlangen-Nürnberg (FAU) from 2019 to 2023. Potential subjects are screened among patients attending pediatric surgical and pediatric gastroenterological clinics. Diagnoses are made according to the ROME IV criteria for FC [12]. Interventions are provided to subjects based on their group assignment of either 3 months of SNM or ENM therapy. Regular checkups and a follow up appointment are conducted within the trial and after 6 and 12 months after the initiation of the intervention. All participants are informed of the purpose of the study and obtain their informed consent before participating in this parallel group study. The subjects may choose to withdraw from the study, or they may be withdrawn from the study, at any time at the discretion of the investigator. If a subject withdraws or is withdrawn, every effort is made to complete and report the observations. The study design is presented in Fig. 3.

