### Recruitment

Participants are recruited from the outpatients and inpatients clinics of the pediatric surgery and gastroenterology departments. Two or more experts determine the eligibility according to the inclusion and exclusion criteria. Informed consent, especially on treatment modalities and off-label use of SNM/ENM in childhood and adolescence, must be obtained before enrollment in the trial by next-of-kin and participants (6 years and older). Thereafter, a baseline assessment is performed, collecting all baseline information relevant to the study (sociodemographic data, medical history, current defecation status). The study schedule is summarized in Fig. 4 and included as the SPIRIT template as Fig. 5. At all timepoints, patients are able to withdraw their participation and end therapy with neuromodulation.

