### Randomization

Participants are enrolled in the study groups at a 1:1 allocation to either the SNM or ENM group. Furthermore, patients are allocated 1:1 stratified based on HD/FC. Enrollment of subjects (assessment of eligibility, patient contact to obtain informed consent) is done by investigators and clinicians prior to randomization. The study design does not allow blinding of the therapist or further analyses in clinical follow-ups. The design is open label with only outcome assessors being blinded, so unblinding will not occur. Data analysis and statistical assessment are conducted separately and anonymously. The statistician performing the statistical analyses is blinded to individual group allocation and treatment.

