#### Primary outcomes and measurement

Primary outcome variables are defined, and change is measured between time points of baseline, 3 and 6 months of therapy as follows:Episodes of abdominal pain: Number of episodes of abdominal pain per weekDefinition of success: reduction by at least 50% of episodes per weekEpisodes of FI: Number of episodes of FI per weekDefinition of success: reduction by at least 50% of episodes per weekDefecation frequency: Number of bowel movements per weekDefinition of success: doubling of episodes per week to at least 3 or more bowel movements per weekStool consistency: Daily assessment of Bristol Stool Scale [16]Definition of success: change of at least 2 points within the scale of 1-7

Patients are classified based on treatment response and efficacy. A “clinically relevant” improvement is defined in cases with at least 2/4 fulfilled criteria, in which symptom control or -reduction is achieved.

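### Outcome times run from the start of treatment, which needs an operation in the SNM arm only, so the baseline-to-month-3 interval may differ by arm and a child who never starts has no month-3 date

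*Protocol article*

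**What the plan says.** **Time origin.** Trial design places the later visits "after 6 and 12 months after the initiation of the intervention". Primary outcomes and measurement says that "change is measured between time points of baseline, 3 and 6 months of therapy as follows". Study objective and hypotheses says "The following hypotheses will be investigated within 3 months of treatment". Study outcomes lists the visits without an anchor: "At routine check-ups at baseline, 4 weeks, 3 and 6 and 12 months, specialized questionnaires must be completed". Nothing in the text dates a visit from randomisation.

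**Baseline and randomisation.** Recruitment puts consent first and then says "Thereafter, a baseline assessment is performed, collecting all baseline information relevant to the study". Randomization says that enrolment ("assessment of eligibility, patient contact to obtain informed consent) is done by investigators and clinicians prior to randomization") comes before allocation. How far baseline lies from randomisation, from the operation or from first stimulation is not stated.

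**Start of treatment.** The technique section says "SNM is applied via two surgical interventions", and that stimulation "will be started on the first postoperative day" after the lead is placed. ENM uses adhesive electrodes and needs no operation. The second SNM operation, 4 weeks later, does not delay the start, because stimulation already runs from the lead implantation.

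**Children without follow-up.** Trial design promises best efforts to complete observations after withdrawal. Statistical analysis carries the last observation forward, and lets the project management group exclude a patient with large amounts of missing data.

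**The concern.** Hypothesis A is a between-arm superiority claim on abdominal pain, judged by change from baseline, in a trial where patients and treating physicians are unblinded. Such a comparison needs the same clock in both arms. Here the clock starts at an event after randomisation that depends on the theatre schedule and the family's willingness in one arm only. Two things follow.

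1. Any wait for lead implantation lengthens the time from baseline to month 3 in the SNM arm alone. Toilet training and maintenance medication continue in both arms, so improvement during the wait would be credited to SNM.
2. A child allocated to SNM who never has the operation never reaches 3 months of therapy. What happens to that child is settled by the missing-data rule and a discretionary decision, not by a visit date fixed in advance.

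At stake is whether the primary contrast compares the two allocated groups over the same period and in full.

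**Working it through.** The article gives no surgical wait and no refusal rate, so there is no stated figure to reproduce on this point. Only the 39 per group is taken from the sample size section. Every wait and every count of never-starters below is an assumption.

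**Step 1: the interval.** Assume that baseline precedes the operation and that ENM starts at once and runs for its stated 12 weeks. Then ENM = 12 weeks, and SNM = wait + 1 day + 12 weeks.

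| Assumed wait (weeks) | SNM interval (weeks) | Excess over ENM |
|---|---|---|
| 0 | 12.14 | 1% |
| 1 | 13.14 | 10% |
| 2 | 14.14 | 18% |
| 4 | 16.14 | 35% |
| 8 | 20.14 | 68% |
| 12 | 24.14 | 101% |

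If baseline is taken just before the start in both arms, the difference is zero whatever the wait.

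**Step 2: what the excess could be worth.** Inputs: the Discussion reports improvement in 39% on conventional options alone and 86% with ENM added, in the group's earlier randomised trial. Assume that the 39% is reached at 13 weeks (about 3 months), that background response accrues at a constant rate, and that neuromodulation is equally effective in both arms.

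- Background response: b(t) = 1 − exp(−kt), with k = −ln(0.61)/13 = 0.0380 per week.
- Arm response: 1 − (1 − b)(1 − q), where q is the added response from neuromodulation. With q = 0.77, ENM is 1 − 0.61 × 0.23 = 86.0%. With q = 0.20, ENM is 1 − 0.61 × 0.80 = 51.2%.
- b(14) = 41.3% and b(15) = 43.5%; b(17), b(21) and b(25) are 47.6%, 55.0% and 61.3%.
- Spurious SNM advantage = [b(13 + wait) − b(13)] × (1 − q).

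| Wait (weeks) | Advantage, ENM at 86% (points) | Advantage, ENM at 51% (points) |
|---|---|---|
| 1 | 0.5 | 1.8 |
| 2 | 1.0 | 3.6 |
| 4 | 2.0 | 6.9 |
| 8 | 3.7 | 12.8 |
| 12 | 5.1 | 17.9 |

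Exact rejection rates of the two-sided uncorrected chi-square test, 39 against 39, when the true effects are equal: with no wait the test already rejects in 5.4% of trials in either scenario. A 1 to 2 week wait gives 5.5 to 5.7% (ENM at 86%) and 5.7 to 6.5% (ENM at 51%). A 4 to 12 week wait gives 6.3 to 11.8% and 9.8 to 36.9%.

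**Step 3: never-starters.** Suppose that 4 of 39 SNM children never start, that treated children respond at 86%, and that ENM is also at 86%. The SNM rate then depends on how the four are handled:

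- Excluded: 86%.
- Assessed, responding at the 39% background rate: (35 × 0.86 + 4 × 0.39)/39 = 81.2%.
- Baseline carried forward, so no response: 35 × 0.86/39 = 77.2%.

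With 8 never-starters the three figures are 86%, (31 × 0.86 + 8 × 0.39)/39 = 76.4%, and 31 × 0.86/39 = 68.4%.

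**Step 4: both effects together.** Even with a 12-week wait, treated SNM children respond at 91.1%. With four never-starters carried forward from baseline, SNM is 0.911 × 35/39 = 81.8%, below ENM at 86%. The net direction is therefore not fixed.

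**The case against.** A reader might infer that SNM children do have a longer interval, that the false-positive rate rises as high as 37%, and that the design always favours SNM. The documents support none of these.

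- **The interval.** No wait and no baseline-to-start window is given. Baseline could be taken shortly before the start in both arms. The schedule figures are not shown and may name an anchor. The full protocol may also hold windows that an article leaves out.
- **The size.** The 39% comes from an arm randomised to an optimisation of conventional options. In this trial these options continue unchanged, in children already refractory to them. It measures general improvement, not a halving of pain episodes, and the article gives it no 13-week time point. The model also treats response as permanent, although weekly episode counts can worsen again. The 37% needs a 12-week wait and an ENM response of 51%, which appears nowhere in the article.
- **The direction.** Carrying baseline forward turns never-starters into SNM failures.
- **The anchor as a choice.** Comparing arms after equal treatment exposure is a legitimate aim. Dating all visits from randomisation would cost SNM stimulation time equal to the wait.

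All of this stands, and it limits the size and direction of the claim. It does not remove the core: the stated origin is the start of treatment, only one arm needs an operation to reach it, and the text sets no month-3 date for a randomised child who never does. The promise of best efforts after withdrawal does not supply that date.

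**Conclusion.** The point holds as a defect in the time origin and in the handling of never-starters, not as a demonstrated bias towards SNM. The interval may be longer in SNM by an unstated wait. The effect is nil with a baseline taken just before the start in both arms. It is about 0.5 to 3.6 points for an assumed 1 to 2 week wait under the constant-rate model. The figures for longer waits are a ceiling, because they rest on a background response observed under optimised care. The never-starter problem needs no assumed wait. With four such children, the SNM rate can lie anywhere from 77% to 86% depending on a rule that mixes carrying forward with discretionary exclusion. The first works against SNM and the second for it. This should be corrected; confidence is moderate, because the wait and the refusal rate are unknown.

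**What to change.** 1. Randomise only once an operating date is available, so that both arms start within the same short window after baseline, and state that window. Alternatively, repeat the baseline diary just before the start in both arms. Either step keeps the comparison at equal treatment exposure.
2. Hold the month-3 assessment for every randomised child. For those who never start, date it from randomisation.
3. Analyse all children in the allocated arm, and remove the project management group's option to exclude a child for missing data.

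The cost is slightly later randomisation and one assessment for each non-starter; the stated sample size does not change. Trial status expected data collection to finish in December 2023, before the article appeared in March 2024, so scheduling may no longer be open to change. In that case the as-allocated analysis still applies, and the report should give the baseline-to-month-3 interval by arm and the number in each arm who never started.
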